# Does the guided online cognitive behavioral therapy for insomnia “i-Sleep youth” improve sleep of adolescents and young adults with insomnia after childhood cancer? (MICADO-study): study protocol of a randomized controlled trial

**DOI:** 10.1186/s13063-021-05263-z

**Published:** 2021-04-26

**Keywords:** Adolescent, Young adult, Childhood cancer, Insomnia, CBT, eHealth, Randomized controlled trial

## Abstract

**Background:**

Adolescents and young adults who had childhood cancer are at increased risk for insomnia, due to being critically ill during an important phase of their life for the development of good sleep habits. Insomnia is disabling and prevalent after childhood cancer (26–29%) and negatively impacts quality of life, fatigue, pain, and general functioning and is often associated with other (mental) health problems. Insomnia and a history of childhood cancer both increase the risk of adverse health outcomes, posing a double burden for adolescents who had childhood cancer. The first-line treatment for insomnia is cognitive behavioral therapy for insomnia (CBT-I). However, access to this type of care is often limited. The guided online CBT-I treatment “i-Sleep” has been developed to facilitate access via online care. i-Sleep is shown effective in adult (breast cancer) patients, but it is unknown if iCBT-I is effective in pediatric oncology.

**Methods/design:**

We developed a youth version of i-Sleep. Our aim is to evaluate its effectiveness in a national randomized-controlled clinical trial comparing iCBT-I to a waiting-list control condition at 3 and 6 months (*n* = 70). The intervention group will be also assessed at 12 months to see whether the post-test effects are maintained. Adolescents and young adults aged 12–30 years with insomnia, diagnosed with (childhood) cancer, currently at least 6 months since their last cancer treatment will be eligible. Outcomes include sleep efficiency (actigraphic), insomnia severity (self-report), sleep and circadian activity rhythm parameters, fatigue, health-related quality of life, perceived cognitive functioning, chronic distress, depressive and anxiety symptoms, and intervention acceptability.

**Discussion:**

Insomnia is prevalent in the pediatric oncology population posing a double health burden for adolescents and young adults who had childhood cancer. If guided iCBT-I is effective, guidelines for insomnia can be installed to treat insomnia and potentially improve quality of life and the health of adolescents and young adults who had childhood cancer.

**Trial registration:**

NL7220 (NTR7419; Netherlands Trial register). Registered on 2 August 2018

## Background

Sleep problems are common after childhood cancer with up to a third reporting significant sleeping disturbance [1, 2]. One particular type of sleep problem which is among the most prevalent ones is insomnia. Insomnia is characterized by difficulty in initiating or maintaining sleep for more than 3 nights a week for more than 3 months which significantly impacts daily life functioning [3]. Insomnia is associated with a lower health-related quality of life (HR-QoL), more fatigue, and worsened psychosocial and neurocognitive functioning [4–8]. In the long run, chronic insomnia is related to increased risk of adverse health outcomes, e.g., musculoskeletal pain, other mental disorders, and cardiovascular disease [9–12]. Childhood cancer survivors are already at increased risk of adverse health outcomes [13]. An additional insomnia diagnosis might therefore pose a double health burden. Furthermore, insomnia developed during childhood tends to become chronic, with up to 88% of adolescents with current insomnia, having a history of insomnia [14, 15]. Adolescents and young adults who had childhood cancer may even be at increased risk for insomnia, being critically ill during a phase of life that is important in the development of good sleep habits [8].

The increased risk of insomnia in adolescents, age-group defined as 12–25 years old [16], and young adults, age-group 19–30 years old [17, 18], who had childhood cancer might be explained within the conceptual model of insomnia: the three-factor (3P-) model. In this model, insomnia develops and is maintained through predisposing, precipitating, and perpetuating factors [19]. Predisposing factors in insomnia entail genetic vulnerability, but also major changes in the sleep architecture that occur during adolescence within circadian and homeostatic bioregulation processes [20]. Other hallmarks of adolescence are also risk factors for insomnia, such as higher stress reactivity and emotional problems due to hormonal changes in puberty, school stress, increased electronic media use, and heightened caffeine intake [21]. All provide a soil for insomnia, which can develop through additional precipitating factors.

Precipitating factors within the context of childhood cancer contain stressful life events, such as the cancer diagnosis and following treatment periods, but also medication and hospitalizations leading to sleep disruption. Being critically ill for a prolonged period of time can lead to change of sleep habits, with e.g. (re)occurrence of daytime napping, increased sleep fragmentation, and less physical activity, which eventually leads to a disruption of the circadian sleep-activity rhythm [8, 22–24]. In general, these sleep problems subside over time. However, not all patients recover. While during treatment up to 75% of patients report sleep problems, after treatment and into survivorship, symptoms remain in 28–29% [1, 2, 25]. In these cases, insomnia is maintained by perpetuating factors, such as the continued disruptive sleeping behaviors and increased hyperarousal. Hyperarousal is a heightened state of distress playing a role in maintaining insomnia and is one of the proposed underlying mechanisms [26]. The context of adolescents and young adults who had childhood cancer therefore entails several risk factors that increase the chance of development and maintenance of insomnia. However, currently, limited interventions for insomnia in adolescents in pediatric oncology are available.

The first-line treatment for insomnia in adults is cognitive behavioral therapy for insomnia (CBT-I), which is effective, shows less side effects, and sustains better long-term effects compared to pharmacological treatments [27, 28]. Compared to adults, the treatment of insomnia in adolescents has been less studied [21, 29]. So far, three randomized controlled trials showed the effectiveness of either face-to-face or online CBT-I for insomnia in adolescents [30, 31]. Furthermore, although there are hypotheses about potential treatment mechanisms of CBT-I for insomnia in adolescents, they are also yet to be validated. In childhood cancer, only one pilot study with a small sample of survivors aged (15–40 years) studied face-to-face and videoconference CBT-I showing adequate feasibility and effectivity [32]. However, even if evidence-based interventions exist, accessibility of those interventions might be low. This is the case for face-to-face CBT-I for insomnia due to a shortage in trained therapists [28]. New developments of online therapy might provide an answer to this problem, having the advantage of flexibility and overcoming geographical boundaries [33]. Online CBT-I (iCBT-I) shows similar effect sizes in treating insomnia in adults compared to face-to-face CBT-I [34]. Additional guidance by an online sleep coach remains important to increase adherence and motivation [35].

The treatment investigated in this study is based on i-Sleep, a guided 5-week iCBT-I program including common CBT-I treatment principles [36, 37]. i-Sleep was shown effective in improving insomnia, and secondary outcomes such as depressive symptoms and HR-QoL, in general population adults in a clinical trial and in an open-cohort study with adult breast cancer patients [38–40]. However, it is unknown if iCBT-I is also effective in adolescents and young adults with insomnia after childhood cancer. We therefore adapted the guided iCBT-I program to fit the adolescent age group and will investigate if “i-Sleep youth” can effectively treat insomnia in adolescents who had childhood cancer.

### Aims and hypotheses

The objective of this trial is to evaluate the effectiveness of the online guided cognitive-behavioral therapy “i-Sleep youth” in treating insomnia in adolescents and young adults who had childhood cancer compared to a waiting-list-control condition in a 1:1 parallel-group superiority RCT. Our hypothesis is that the intervention will improve sleep efficiency (actigraphy) and insomnia severity (self-report) on the short-term compared to the control group, which is maintained on the long-term up to a year after the intervention. Furthermore, we expect that patients in the intervention group will also show improvement on other actigraphy-based sleep parameters (sleep onset latency, wake after sleep onset, total sleep time). We will also assess two non-parametric circadian rhythm parameters, in which we expect that the intervention group will show increased stability and less fragmentation of the 24-h sleep-activity rhythm. Other outcomes we hypothesize to be improved after the intervention are HR-QoL, fatigue, (perceived) cognitive functioning, and depressive and anxiety symptoms compared to the control group. We also aim to study the acceptability of the online intervention in the adolescent target group. At last, we aim to explore the treatment mechanism in this population by studying the following mediators: chronic hyperarousal (defined as chronic distress) and disrupted daytime rhythm (napping). These mediating treatment factors were found in CBT-I for adult insomnia populations [41] and might also be mediating factors in treating insomnia after childhood cancer (higher chronic distress and disrupted rhythm due to being ill).

## Methods/design

### Study design

The MICADO-study (Managing Insomnia after Childhood cancer in ADOlescents) is a national randomized controlled clinical trial. The trial will be coordinated from the Princess Máxima Center for pediatric oncology, which is the single national pediatric cancer center in the Netherlands. Patients with insomnia during pediatric cancer follow-up or survivor care will be randomized to either immediate access to the online intervention or the waiting-list control group. Participants in the waiting-list control group will receive the online treatment after 6 months. The design of the trial and study flow is shown in Fig. 1. This trial has been approved by the Medical Ethics Committee of UMC Utrecht (NL65009.041.18) and registered at the Netherlands National Trial Register (Trial NL7220 (NTR7419)). Patient inclusion started in January 2019.

**Fig. 1 Fig1:**
[figure not shown]
Design of the trial and study flow

### Participants: inclusion and exclusion criteria

Patients are eligible when they fulfill the following criteria: have insomnia symptoms of at least subthreshold clinical severity (Insomnia Severity Index-score ≥ 8; ISI, see the “Outcomes” section), aged between 12 and 30 years old, diagnosed with (childhood) cancer or a low-grade brain tumor and at least 6 months since their last cancer treatment (since insomnia during treatment can be directly related to therapy and recover spontaneously). Exclusion criteria are (a) receiving palliative therapy; (b) not sufficiently fluent in Dutch; (c) significant cognitive impairment; (d) comorbidities that affect sleep or can be exacerbated by the sleep restriction in CBT-I, e.g., severely diminished eye-sight (sleep-wake rhythm can be affected due to poor sight), acute schizophrenia or substance abuse, history of a seizure disorder diagnosis or having experienced a seizure within the past 12 months; (e) pregnancy or patients who just had a newborn < 6 months, since sleep problems often occur in pregnancy and parents of a newborn; (f) shift work employment; (g) suicidality; (h) current psychological treatment for psychopathology (e.g., substance abuse, psychosis) or sleeping disorders; and (i) severe sleep disorders other than insomnia and untreated sleep-breathing disorders (SBD). Patients that use sleep medication such as benzodiazepines and melatonin will not be excluded since they may still benefit from the intervention. The use of sleep medication will, however, be monitored throughout the study, as a secondary outcome of the intervention.

### Description of the guided online CBT for insomnia intervention: i-Sleep youth

I-Sleep is an online therapy to treat insomnia based on common CBT-I principles with non-synchronous online guidance by a sleep coach. The Internet intervention is developed at the Vrije Universiteit (author [name]) based on CBT-I protocols including psycho-education, stimulus control, sleep restriction, relaxation, and cognitive restructuring. These elements are offered in 5 sessions in 5–8 weeks through written texts, videos, patients vignettes, and exercises. A sleep diary app is complimentary used to guide the monitoring the sleep behavior and sleep restriction. For more information about the development of the original intervention, see Van Straten et al. [40]. The topics of the five lessons and intervention flow are shown in Fig. 2. The intervention is weekly guided by an online coach with a psychosocial background supervised by a sleep expert. We adapted the original version of i-Sleep into “i-Sleep youth” to accommodate the target group adolescents (12–30 years) after childhood cancer. The instruction text, videos, logo, images, and four patient vignettes (two video and two written vignettes per session) were adjusted to adolescent language use and examples entailing both younger adolescent stories including going to school, as older adolescents who just started studying or working. Age-appropriate themes were added: attention for screen use, gaming, drugs, and energy drinks [21]. As parents play a key role in the life of mainly the younger adolescents, an intervention factsheet for parents with a summary and support tips was developed. Within the Dutch law of Agreement on Medical Treatment Act, adolescents who are 16 years or older are considered competent to enter a medical agreement independently. Therefore, within i-Sleep youth, the factsheet is optional for adolescents above 16 years of age. Parents of 13–15 years olds will automatically receive the factsheet. After the adaptation phase, i-Sleep youth was evaluated on target-group suitability and usability by three independent child-sleep experts, the Dutch childhood cancer parent-patient organization, and eight adolescents in a suitability and usability evaluation. The evaluation results were used for the final adjustments of i-Sleep youth.

**Fig. 2 Fig2:**
[figure not shown]
The topics of the five lessons and intervention flow

#### Control group: waiting list condition

Patients in the control group will be randomized to a waiting list of 6 months after which they are offered the intervention. They are asked not to seek treatment for sleeping problems (either behavioral or pharmacological) during the waiting period. Adherence to this request will be assessed at follow-up time points. After 6 months they will be offered the intervention on which they will provide feedback via an intervention feedback questionnaire and contribute to studying intervention acceptability. The effectiveness of i-Sleep will not be assessed in this group.

### Assessments

The outcomes will be evaluated at baseline (T0), 3 months (T3), and 6 months (T6) after randomization. Patients in the intervention will additionally be assessed at 12 months (T12). See Table 1 for an overview of assessments. Acceptability of i-Sleep will be measured following the intervention. All self-report questionnaires will be offered through a secure website, www.hetklikt.nu. This secure internet environment is in use in patient care as well as in pediatric (oncology) care in the Netherlands [42, 43]. Paper questionnaires will be available upon request to the participants. The baseline choice of modality (paper-pencil or online) will be retained for all time points.

**Table 1 Tab1:** Study outcome measurements and time points

Measurement	Instrument	Nr. of items	Time-points			
			Baseline (T0-months)	Post treatment (T3 months)	Follow-up T6 months	Follow-up T12* months
**Primary outcomes**						
Sleep efficiency (SE)	Actigraph and sleep log	–	X	X	X	X
Insomnia Severity	ISI	7	Assessed in screening	X	X	X
**Secondary outcomes:**						
Sleep parameters: TST, TTB, SOL, WASO, napping	Actigraph and sleep log		X	X	X	X
Circadian rhythm parameters: Fragmentation (IV) and intradaily stability (IS)	Actigraph and sleep log		X	X	X	X
Health-Related (HR) quality of life	PedsQL - teens 13–18 years - young adult 19–30 years	23	X	X	X	X
Fatigue	CIS	20	X	X	X	X
Depressive and anxiety symptoms	HADS	14	X	X	X	X
Perceived cognitive functioning	Peds-PCF-SF	10	X	X	X	X
Chronic stress	CSQ-CA	19	X		X	X
General questionnaire	Pain Sleep medication use	2	X	X	X	X
Intervention feedback	Satisfaction questionnaire, adherence	20		X*/X**		

Notes.*only intervention-condition, **at 9 months for control-condition. *TST* total sleep time, *TTB* total time in bed, *SOL* sleep onset latency, *WASO* wake after sleep onset, *ISI* Insomnia Severity Index, *CIS* Checklist Individual Strength, *HADS* Hospital Anxiety and Depression Scale, *Peds-PCFSF* Peds Perceived Cognitive functioning Short Form, *CSQ-CA* Chronic Stress Questionnaire for Childs and Adolescents

### Outcomes

#### Primary outcomes

##### Sleep efficiency (SE)—based on actigraphy

Sleep efficiency (SE) based on a 7-day wrist actigraphy measurement is a primary outcome of this trial. SE can be calculated by dividing total sleep time (TST) by the total time the person spent in bed (× 100%). SE contains information on difficulties falling asleep as well as difficulties staying asleep and is therefore often considered the best primary outcome measure as it represents different types of sleep problems [44]. Average SE throughout the week will be calculated using information gathered from the actigraph and accompanied sleep log [45]. For more information on actigraphy methods, see paragraph “sleep parameters.”

##### Insomnia severity—self-report questionnaire

*Insomnia severity* is additionally a primary outcome and will be evaluated using the Insomnia Severity Index (ISI) [46]. The ISI is a 7-item self-report questionnaire that assesses the nature, severity, and impact of insomnia. The dimensions are severity of sleep onset, sleep maintenance and early morning waking problems, sleep dissatisfaction, interference of sleep difficulties with daytime functioning, noticeability of sleep problems by others, and distress caused by sleep difficulties. It is rated on a 5-point Likert scale (total score 0–28). A score of 0–7 indicates absence of insomnia, 8–14 sub-threshold insomnia, 15–21 moderate insomnia, and 22–28 severe insomnia. Internal consistency is excellent in community as well as clinical samples (Cronbach’s alpha 0.90–0.91). Acceptable reliability is shown in cancer survivors [47]. A decrease of 8 points is considered a relevant clinical change in insomnia severity [46].

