### Statistical analyses

Intention-to-treat as well as per-protocol analysis will be performed. A linear regression model adjusted for baseline score will be estimated to answer our primary study aim: the effectiveness of iCBT-I on SE and insomnia severity (ISI-score) in the iCBT-I group and the WL posttreatment (T3). The differences in SE and ISI at T3 between both groups will also be expressed in Cohen’s d effect sizes. For our secondary study aims, the clinical relevant response from the intervention effect posttreatment will be investigated by estimating a logistic regression model using yes/no clinical improvement based on the self-reported insomnia severity, since this represents both sleep problems, as daytime consequences of insomnia. A clinically relevant improvement is defined based on the self-report ISI as a decrease of ≤ 8 points between T0 and T3 [46, 67]. Due to the presence of repeated measurements a mixed linear model will be estimated to investigate the long-term effects. Mediation analyses at T3 are performed with the regression-based PROCESS macro [69] in which the potential mediational effect of chronic stress and napping on treatment effectivity on SE and ISI at T3 is tested. Missing data will be imputed under the appropriate missing data analysis assumptions, e.g. leading to multiple missing data imputation [70]. All analyses will be performed using SPSS and R.

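### The ISI responder rule is printed with its inequality reversed; once corrected, it still classes some sub-threshold entrants who reach the no-insomnia band as not improved.

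*Protocol article*

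**What the plan says.** The eligibility section of the protocol article admits patients who "have insomnia symptoms of at least subthreshold clinical severity", set at an ISI of 8 or more. The outcome section on insomnia severity gives the bands: "A score of 0–7 indicates absence of insomnia, 8–14 sub-threshold insomnia, 15–21 moderate insomnia, and 22–28 severe insomnia". It then states: "A decrease of 8 points is considered a relevant clinical change in insomnia severity".

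The Statistical analyses section assesses clinically relevant response, as a secondary aim, by "estimating a logistic regression model using yes/no clinical improvement based on the self-reported insomnia severity". The operative definition there reads: "A clinically relevant improvement is defined based on the self-report ISI as a decrease of ≤ 8 points between T0 and T3". This is the only binary efficacy outcome the article states, and the article gives no criterion based on the ISI score reached at T3.

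The primary ISI analysis is separate. It is a linear regression of the T3 score adjusted for baseline.

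**The concern.** There are two linked faults.

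First, the outcome section and the analysis section disagree on the direction of the threshold. Anyone programming the analysis section as printed would build a variable that is close to the reverse of response.

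Second, correcting the sign exposes a mismatch with eligibility. A fixed 8-point fall is a demanding target for a patient who enters at 8, 9 or 10, because there is little scale left below. For every entry score from 8 to 14 the rule is stricter than reaching the protocol's own no-insomnia band. A patient who goes from 14 to 7 no longer has insomnia by those bands but is a non-responder. A patient who goes from 22 to 14 still has sub-threshold insomnia but is a responder.

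At stake is how the trial's one binary statement on clinical relevance is read, in a population that deliberately includes sub-threshold cases.

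**Working it through.** **Inputs from the protocol article**
- Entry: ISI ≥ 8 (eligibility; recruitment). Table 1 shows that the baseline ISI is the screening score.
- Scale 0–28; bands 0–7 none, 8–14 sub-threshold, 15–21 moderate, 22–28 severe (outcome section).
- Relevant change: a fall of 8 points (outcome section).
- Responder rule as printed: a fall of ≤ 8 points from T0 to T3 (Statistical analyses).

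The protocol gives no responder rate or ISI distribution, so there is no stated figure to reproduce here. The sample size rests on sleep efficiency and does not use this rule.

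**Step 1. The rule as printed.** Let b be the entry score, e the T3 score and d = b − e. Improved if d ≤ 8:
- no change, d = 0: improved;
- 22 to 14, d = 8: improved;
- 17 to 8, d = 9: not improved;
- 16 to 0, d = 16: not improved.

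This cannot be what is meant, and it conflicts with the outcome section.

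**Step 2. The rule with the sign corrected.** Improved if b − e ≥ 8, that is, e ≤ b − 8.

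| Entry b | T3 score needed | T3 scores in 0–7 that fail | Number failing, of 8 |
|---|---|---|---|
| 8 | 0 | 1–7 | 7 |
| 9 | ≤ 1 | 2–7 | 6 |
| 10 | ≤ 2 | 3–7 | 5 |
| 11 | ≤ 3 | 4–7 | 4 |
| 12 | ≤ 4 | 5–7 | 3 |
| 13 | ≤ 5 | 6–7 | 2 |
| 14 | ≤ 6 | 7 | 1 |
| ≥ 15 | ≤ 7 or higher | none | 0 |

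Total failing at entry 8–14: 7 + 6 + 5 + 4 + 3 + 2 + 1 = 28, of 7 × 8 = 56 pairs. This counts score pairs, not patients. The mismatch disappears at entry 15 and above.

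**Step 3. Illustrative share of patients.** The inputs here are assumptions, not protocol figures: entry ISI normal with SD 4, truncated at 8; mean change −6 in the iCBT-I arm; residual SD 4; scores rounded and kept within 0–28. Share of sub-threshold iCBT-I entrants who end at 0–7 but fall by fewer than 8 points:
- entry mean 12 before truncation: about 34%;
- entry mean 14: about 31%;
- entry mean 16: about 27%.

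Depending on rounding conventions, the range is about 27% to 35%.

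With the denominator changed to sub-threshold entrants who reach 0–7, and a wider set of assumptions (entry mean 11–17, mean fall 4–8, SD of change 4.5), about 28% to 60% would be non-responders.

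**The case against.** The strongest reply is that change and end status are different quantities. The protocol chose change, cites sources for its threshold, and is entitled to do so; a supportive remission outcome might sit in the full protocol or analysis plan. This stands in part. The 8-point response is a legitimate measure and should be kept. But the article itself fixes the rule and the entry criterion, and the two fit badly at entry scores 8–14. The reversed sign is an error in the printed text on any view.

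It is also fair that the analysis is secondary. The primary ISI analysis is continuous, so a fall from 14 to 7 is credited there in full.

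A reader might infer three stronger things that the documents do not support:
- **That all sub-threshold remitters fail.** They do not: 14 to 6, 12 to 4 and 10 to 2 are all responses.
- **That the response rate would mainly reflect severity at entry.** With a constant mean change of −6, the simulated response is about 35% in both entry bands. A gradient (about 22% at entry 8–10 against 44% at 15 or more) appears only if larger falls at higher entry scores are assumed, for example a T3-on-entry slope of about 0.7. The protocol gives no basis for that.
- **That the 8-point rule loses power against remission.** With 28 per arm (35 × 0.8), baseline-adjusted likelihood-ratio tests gave 87% for the 8-point rule and 85% for remission at entry mean 14, and 85% against 74% at mean 16. Wald tests gave 59% against 79% at mean 14 and 57% against 26% at mean 18. The order depends on the test and the case mix.

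**Conclusion.** The point holds in two parts. The contradiction between the outcome section and the Statistical analyses section is certain and must be reconciled, evidently to a fall of at least 8. Under that reading it is also certain that some, not all, sub-threshold entrants who reach the no-insomnia band count as not improved: half of the possible score pairs, most heavily at entry 8 to 10.

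How many patients this concerns cannot be derived from the protocol. The 27% to 35% rests wholly on the assumed entry distribution, mean change and residual SD.

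The primary analyses of continuous ISI and sleep efficiency, and the sample size, are unaffected. Nothing is concluded about power or about a response gradient by entry severity. Correcting the sign is necessary; the remission outcome is a cheap improvement.

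**What to change.** 1. In Statistical analyses, correct the definition to a decrease of at least 8 points between T0 and T3, in line with the outcome section.
2. Keep this as the cited response measure.
3. Before analysis, pre-specify remission at T3 (ISI 0–7, the protocol's own no-insomnia band) as a second secondary binary outcome, in the same logistic model with baseline ISI as covariate.
4. Describe the 8-point response separately for entry ISI 8–14 and ≥ 15, without testing between bands, and base the statement on clinical relevance on response and remission together.

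The cost is one more secondary comparison and a few lines of text. No new data are needed, since the ISI is already collected at T3.
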